#### Saliva collection and measurement of markers of inflammation

Participants will rinse with 85 mL of water for approximately 1 min, 10 min prior to collection. Saliva will be collected using unstimulated passive drool and a saliva collection aid (Salimetrics; Carlsbad, CA) into a prelabeled collection vial. Saliva samples will be stored on ice in a small cooler, centrifuged at 3000*g* for 15 min and supernatant collected into a labeled sterile tube and stored at − 80 °C until analysis. IL-1ß, IL-6, and CRP will be analyzed using enzyme-linked immunosorbent assay kits (Salimetrics; Carlsbad, CA) and MMP-8 will be analyzed using a human quantikine enzyme-linked immunosorbent assay kits (R&D Systems, Inc.; Oakville, Canada) as per the manufacturer’s instructions. All assays will be completed in triplicate.

#### Periodontal-associated pathogens

Participants will rinse with saline for 30 s then expectorate spit in a collection tube. This sample will be taken after the saliva sample that will be used for the measurement of markers of inflammation. Samples will be frozen at -80 °C until further analysis. *A. actinomycetemcomitans*, *P. gingivalis*, *T. forsythia*, and *T. denticola* will be quantified by quantitative PCR [28].

#### Dietary assessment

Dietary intakes will be measured using the Canadian version of the Automated Self-Administered 24-hour (ASA24®) Dietary Assessment Tool. The ASA24 will be completed online by participants and food intakes will be recalled over a 24-h period. ASA24 features two web-based applications, one that the participant will use to complete dietary recalls and one for the researcher to access nutrient analyses. Participants will be asked to complete 3 dietary assessments at each visit time point (two weekdays and one weekend day) to obtain an accurate representation. Participants will be given their username and password for the ASA24 respondent website so that they can complete the dietary assessments at home. The username will match their unique code administered on the intervention package. Participants will complete the first set of recalls before they begin the intervention. For Visits II and III, the research team will email or call the participant a week before their upcoming appointment and instruct them to log on to the ASA24 website and complete a set of food recalls before they return to the clinic for their next visit. Total energy intake, protein, fat, and carbohydrate intakes will be extrapolated from the assessments for the analysis. The means of each nutrient will be taken from the 3 recalls for each visit.

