**Methods:**

We will employ a single-center, randomized, double-blind, placebo-controlled study design and recruit and randomize 170 participants who are receiving ST to manage the periodontal disease to the intervention (inulin) or placebo (maltodextrin) group. A pilot study will be embedded within the randomized controlled trial using the first 48 participants to test the feasibility for the larger, powered trial. The intervention period will begin 4 weeks before ST through to their follow-up appointment at 10 weeks post-ST. Clinical outcomes of periodontal disease including the number of sites with PD ≥ 4 mm and the presence of BOP will be measured at baseline and post-ST. Salivary markers of inflammation, periodontal-associated pathogens, body mass index, and diet will be measured at baseline, pre-ST (after 4 weeks of intervention), and post-ST (after 14 weeks of intervention).

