**Fig. 2 Fig2:**
[figure not shown]
Study design flowchart

The visits and timeline is described below:
Visit 0 (virtual visit): Eligibility screening and informed consent will follow if the participant meets the criteria.Visit I (initial consult): Informed consent (if not given virtually at Visit 0). Randomization to either inulin or placebo group. Baseline periodontal assessment (PD and BOP), anthropometry (weight, height), dietary assessment, salivary markers of inflammation, and periodontal-associated pathogensVisit II (ST is performed): Anthropometry (weight, height), dietary assessment, salivary markers of inflammation, and periodontal-associated pathogens. ST is typically scheduled 4 weeks from the patient’s initial consultation.Visit III (follow-up, post-ST): Final periodontal assessment (PD and BOP), anthropometry (weight, height), dietary assessment, salivary markers of inflammation, and periodontal-associated pathogens.

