### Implementation {16c}

The inulin or placebo will be prepared ahead of time and stored at the clinic. The packaging will ensure that the specific treatment cannot be visually ascertained. The participants will be randomized to receive a package at the clinic and the unique code on the package will become the code that identifies the participant. Participants will be instructed to use this code to complete their dietary assessments at home. This code will also be used to label saliva samples. At this time, participants will receive verbal instructions on how to take the supplement and ask any questions they might have. Written instructions will also be included in the package to refer to when they are back home.

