### Methods in analysis to handle protocol non-adherence and any statistical methods to handle missing data {20c}

We want to ensure the treatment effect is not conservative; therefore a modified-to-treat approach will be used in the analysis of this trial. To be included in the analysis, participants will need to take the intervention for 75% of the 28 days pre-ST and for 75% of the 70 days post-ST. The study protocol is designed to maximize data collection. Missing data for secondary outcomes, particularly dietary intakes, the statistical method of multiple imputation will be used.

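### Baseline recalls delay the first sachet, so with sanative therapy (ST) at the typical 4 weeks from Visit I the 75% adherence rule counts 28 pre-ST days when fewer exist (minor)

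*Protocol article*

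**What the plan says.** - **Code and package.** The visit list under Trial design {8} places this step at Visit I: "Randomization to either inulin or placebo group". Implementation {16c} says participants are "randomized to receive a package at the clinic and the unique code on the package will become the code that identifies the participant", and that they use this code for their dietary assessments at home.
- **Recalls.** Dietary assessment asks for three recalls per time point, on two weekdays and one weekend day. On the login it says: "The username will match their unique code administered on the intervention package". On timing it says: "Participants will complete the first set of recalls before they begin the intervention".
- **Timing of ST.** The visit list says "ST is typically scheduled 4 weeks from the" initial consultation. The Abstract (Methods) says: "The intervention period will begin 4 weeks before ST through to their follow-up appointment at 10 weeks post-ST". It also labels the Visit II measurements as taken after 4 weeks of intervention.
- **Analysis rule.** Section {20c} says that, to be analysed, "participants will need to take the intervention for 75% of the 28 days pre-ST" and for the same share of the 70 days after ST.

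**The concern.** Two clocks are in use. The visit list counts the 4 weeks to ST from Visit I. The Abstract and the adherence rule count 4 weeks from the start of the intervention. The two agree only if the first sachet is taken at Visit I, and the recall requirement prevents that.

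Section {20c} makes the 75% rule a condition for being in the analysis, with no exception for the primary outcome. If the 28 is applied as written while fewer dosing days exist, the rule demands more than 75%. Participants with adequate adherence could then be dropped for a reason unrelated to their behaviour. They would come out of the margin in Sample size {14}, which is 85 − 71 = 14 per group for all losses. The pre-ST period that the Discussion uses to judge inulin alone would also be somewhat shorter than 4 weeks and would vary between participants.

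**Working it through.** **1. The plan's own figures.** 0.75 × 28 = 21 dosing days required, so 28 − 21 = 7 misses allowed. 28 + 70 = 98 days = 14 weeks, which matches the stated length of the intervention. The figures are consistent if dosing starts exactly 28 days before ST.

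**2. Earliest first sachet.** The protocol does not state the delay, so I derived it. Assumptions: Visit I falls on Monday to Friday; each recall covers the previous day; the three recalls are done as early as the two-weekday, one-weekend-day rule allows. Delay in days from Visit I to the day the last recall is completed:

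| First recalled day | Mon | Tue | Wed | Thu | Fri |
|---|---|---|---|---|---|
| Day before Visit I | 2 | 5 | 4 | 3 | 2 |
| Day of Visit I | 6 | 5 | 4 | 3 | 4 |
| Day after Visit I | 6 | 5 | 4 | 5 | 5 |

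Dosing may start that day or the next (+1), which gives 30 combinations. The delay is 2 days in 2 of them, 3 in 4, 4 in 6, 5 in 9, 6 in 7 and 7 in 2. A delay of 3 to 6 days therefore arises in 26 of 30. The combinations are unweighted, so these counts are not probabilities.

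**3. Days available with ST on day 28.** With delay d, the dosing days are n = 28 − d. The share required by the rule is 21/n, and the misses allowed are n − 21. With the actual days as denominator, the doses needed are 0.75n rounded up.

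| d | n | 21/n | Misses allowed | Doses needed on actual days | At least 75% of n, yet excluded |
|---|---|---|---|---|---|
| 3 | 25 | 84.0% | 4 | 19 | 19–20 doses (76.0–80.0%) |
| 4 | 24 | 87.5% | 3 | 18 | 18–20 doses (75.0–83.3%) |
| 5 | 23 | 91.3% | 2 | 18 | 18–20 doses (78.3–87.0%) |
| 6 | 22 | 95.5% | 1 | 17 | 17–20 doses (77.3–90.9%) |

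The extremes are d = 2 (26 days, 80.8%, 5 misses) and d = 7 (21 days, 100%, 0 misses).

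**4. Illustration only.** The protocol gives no adherence figure. Assume 24 available days and independent daily adherence p, with doses taken following Binomial(24, p).

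| p | Fail as written, P(X < 21) | Fail on actual days, P(X < 18) |
|---|---|---|
| 0.95 | 3.0% | 0.0% |
| 0.90 | 21.4% | 0.7% |
| 0.85 | 49.5% | 5.7% |

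This shows that the denominator can matter. It does not estimate the loss in this trial.

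**The case against.** The strongest reply is that the protocol already gives the right clock. The Abstract ties the start of the intervention to 4 weeks before ST, and Dietary assessment separates the baseline recalls from that start. On this reading the 28 days run from first sachet to ST, and the line about 4 weeks from the consultation only describes usual clinic booking. An ST a few days later satisfies every statement at once. This stands in part: the conflict is confined to the typical schedule, and it would be wrong to say that nothing links the start of dosing to ST. It does not remove the point. The section on retention {18b} says the intervention was designed around the clinic's existing appointments, and nothing in the text shown moves ST to allow for the recalls.

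It is also fair to say that the participant timeline table and the flowchart are not shown and may settle this, and that staff might treat 28 as a nominal figure. As written, however, the rule names 28.

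A reader might infer more than the documents support:
- **That the rule leaves no room for a miss or cannot be met.** Zero misses needs a 7-day delay, which occurs in 2 of the 30 prompt-recall combinations. The rule becomes unreachable only with a delay over 7 days, ST on exactly day 28 and a literal count of 28.
- **That a fifth or a half of participants would be lost.** Those percentages rest on an assumed adherence, an assumed delay and independence between days.
- **That the comparison is biased.** The shortening comes from a schedule common to both blinded arms and does not by itself favour either.

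**Conclusion.** The point holds in a limited form. When ST falls at the typical 4 weeks from Visit I, the requirement to finish the recalls first leaves fewer than 28 pre-ST dosing days, most often about 22 to 25 (3.1 to 3.6 weeks). The fixed denominator then turns a 75% threshold into one of about 84% to 95%, and some adequately adherent participants would be excluded.

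This rests on three assumptions: recalls done promptly after a weekday Visit I, ST at day 28, and the 28 taken literally. A later ST or a nominal reading of the 28 removes the effect. The number excluded cannot be estimated from the protocol. It is probably small, and the shortening is expected to be equal in both arms. Severity is minor.

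**What to change.** Record the date of the first sachet. In section {20c}, replace the fixed 28 with the actual number of days from first sachet to ST, and the fixed 70 with the actual number of days from ST to follow-up. The 75% threshold then means what it says whatever the booking dates.

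Optionally, book ST at least 28 days after the first sachet where the clinic schedule allows, which would also make the description of Visit II as after 4 weeks of intervention accurate.

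The cost is one recorded date and two changed denominators. With the optional booking, ST would fall a few days later for some patients. Supply is sufficient at the planned intervals: 28 + 70 = 98 days from the first sachet, against 100 sachets per participant (Strategies to improve adherence {11c}).

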#### Anthropometric assessment

Height and weight will be measured to calculate BMI (kg/m^2^). Participants will be asked to remove their shoes and will be weighed and height will be measured to the nearest 0.1 kg and 0.1 m, respectively, using a height and weight scale (Health-O-Meter Professional; Sunbeam Products, Inc.). If certain situations prevent height and weight from being taken (COVID-19 pandemic), we will use self-reported height and weight.

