### Methods for additional analyses (e.g., subgroup analyses) {20b}

The study will also determine if there is a difference in the effect of inulin on the primary outcomes in terms of BMI. Subgroup analyses for the number of sites with PD ≥ 4 mm will be performed using two categories for BMI: normal BMI (< 25 kg/m^2^) or overweight/obese (≥ 25 kg/m^2^). This analysis will be conducted using an independent sample *t* test. Chi-square analyses will be performed for BOP.

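### Height is specified to the nearest 0.1 m (10 cm), very probably a unit slip; followed as written, it blurs the BMI 25 subgroup and could distort change in BMI

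*Protocol article*

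**What the plan says.** The section Anthropometric assessment gives the purpose of the measurements: "Height and weight will be measured to calculate BMI (kg/m^2"). It then gives their precision: participants "will be weighed and height will be measured to the nearest 0.1 kg and 0.1 m, respectively". The last word of that quote ties 0.1 kg to weight and 0.1 m to height. The same section adds that if circumstances such as the pandemic prevent measurement, "we will use self-reported height and weight".

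The visit list under Trial design {8} has height at every visit. Visit I has "Baseline periodontal assessment (PD and BOP), anthropometry (weight, height), dietary assessment", Visit II has "Anthropometry (weight, height), dietary assessment, salivary markers of inflammation, and periodontal-associated pathogens. ST is typically scheduled 4 weeks" after the initial consultation, and Visit III has "Final periodontal assessment (PD and BOP), anthropometry (weight, height), dietary assessment".

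Two planned analyses use the resulting BMI. Secondary outcome measures lists change in BMI. Methods for additional analyses {20b} splits participants into "two categories for BMI: normal BMI (< 25 kg/m^2^) or overweight/obese (≥ 25 kg/m^2") for both primary outcomes, and the Discussion predicts a larger response in the overweight/obese group.

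No other place in the document gives a finer height unit or says which visit's height is used to calculate BMI.

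**The concern.** With 0.1 m precision, adults can only be recorded as 1.5, 1.6, 1.7, 1.8 m and so on. BMI divides by height squared, so an error of up to 5 cm in height becomes an error of roughly 5-7% in BMI at the rounding edges. Two things are at stake.

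- **Subgroup.** BMI is the only subgroup factor and is cut at exactly 25 kg/m². Participants near the cut could be placed on the wrong side.
- **Change in BMI.** Adult height is effectively constant over 14 weeks. If height is re-recorded at each visit and rounds differently, BMI appears to change with no change in weight.

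Precision lost when height is recorded cannot be recovered at analysis.

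**Working it through.** The plan derives no figure from the height precision, so there is no result to reproduce. The check works out what the stated precision implies.

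**Inputs from the protocol:** height to 0.1 m and weight to 0.1 kg (Anthropometric assessment); cut at 25 kg/m² (Methods for additional analyses); height listed at Visits I, II and III (Trial design); 71 participants needed per group, so 142 in all (Sample size for full trial).

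**1. Error at the cut (needs no assumption).** Recorded BMI = true BMI × (true height / recorded height)². For a true BMI of 25:

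| True height | Recorded height | Recorded BMI |
|---|---|---|
| 1.65 m | 1.7 m | 25 × (1.65/1.7)² = 23.55 |
| 1.75 m | 1.7 m | 25 × (1.75/1.7)² = 26.49 |
| 1.75 m | 1.8 m | 25 × (1.75/1.8)² = 23.63 |

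The error is about ±1.5 kg/m². It is slightly larger for shorter people: at 1.55 m recorded as 1.5 m, 25 × (1.55/1.5)² = 26.69.

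**2. Share in the wrong subgroup (simulation, 1,000,000 people).** Assumptions, none of them in the protocol: half men and half women; height mean/SD 1.76/0.07 m and 1.62/0.065 m; three BMI distributions.

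| BMI mean/SD | Wrong side of 25, height to 0.1 m | to 0.01 m | to 0.001 m |
|---|---|---|---|
| 25/4 | 7.3% | 0.75% | 0.11% |
| 27/5 | 5.4% | 0.56% | 0.08% |
| 29/6 | 4.0% | 0.40% | 0.06% |

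A second simulation (height mean 1.70 m, SD 0.09-0.10; BMI mean 26-30, SD 4.5-6) gave 3.4-6.3% at 0.1 m. Over both, the range is about 3-7%. Among 142 participants that is 142 × 0.034 ≈ 5 to 142 × 0.073 ≈ 10 people.

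**3. Change in BMI if each visit's own height is used.** A person of 75 kg whose recorded height moves one step shows a change with no change in weight:

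- 75/1.6² − 75/1.7² = 29.30 − 25.95 = 3.35 kg/m²
- 75/1.7² − 75/1.8² = 25.95 − 23.15 = 2.80 kg/m²

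How often this happens depends on the repeatability of the height measurement. The next table uses the simulation of step 2 with an assumed SD of true weight change of 2 kg, which gives a true SD of BMI change of 0.71 kg/m².

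| Assumed SD of repeat height error | Participants changing step between two visits | SD of recorded BMI change |
|---|---|---|
| 0.3 cm | 3.4% | 0.90-0.96 |
| 0.5 cm | about 5.6% | 1.01-1.10 |
| 1 cm | about 11% | 1.24-1.38 |

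**4. Change in BMI if the recorded height is the same at every visit.** The SD of the error in change is about 0.03 kg/m², even at 0.1 m precision.

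**5. Correcting the unit alone.** With height to 0.001 m but re-measured at each visit, and a repeat error of SD 0.5 cm, the SD of the error in change is still 0.21-0.25 kg/m². Using one height removes that as well.

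**The case against.** The strongest reply is that 0.1 m is a slip of the pen. The protocol names a professional height and weight scale, and nobody plans to record adult height in 10 cm steps. If staff record to 0.1 cm, misclassification is about 0.1% and the matter is editorial. This is very probably right. What stands against it is that the sentence is a measurement instruction, not background, and nothing else in the document corrects it.

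A second reply is that the article does not say each visit's height enters that visit's BMI. Which height is used is a detail that a condensed article may leave to the full protocol or analysis plan, and the schedule in Table 2 is not shown. This stands. The artefact in change in BMI is therefore conditional.

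Three stronger readings are tempting, and the documents do not support them.

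- **That the subgroup analysis becomes unusable.** Most participants stay correctly placed, and those misplaced lie close to 25. As an illustration, with half the sample below 25 and 5% misplaced in each direction, a subgroup contrast shrinks by a factor of 1 − 2 × 0.05 = 0.90.
- **That the artefact exceeds any plausible 14-week effect on BMI.** The protocol gives no expected change in BMI. The Discussion cites a decrease in patients with type 2 diabetes without a figure.
- **That self-reported height and weight are a further error.** They are a disclosed fallback, limited to situations that prevent measurement. Excluding such values from the analysis of change would discard data and could introduce selection.

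**Conclusion.** The stated height precision is wrong as written and should be corrected. The certainty attaches to the wording; whether the trial's data will carry 10 cm rounding is unknown, and they probably will not.

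If the instruction is followed literally, the error of about ±1.5 kg/m² at the cut follows directly from the protocol's own figure. The 3-7% misclassification rests on assumed height and BMI distributions. The spurious change of about 3 kg/m² applies only to participants near a rounding edge, and only if each visit's own height is used; its frequency of 3-11% rests on an assumed repeat error of 0.3-1 cm.

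Rounding does not depend on arm, and participants and care providers are blinded. The effect is therefore added noise and a blurred subgroup, not bias between arms. The main analysis of the primary outcomes does not use BMI and is untouched.

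**What to change.** In Anthropometric assessment, change the height precision to the nearest 0.1 cm (0.001 m). Add one sentence saying that BMI at all three visits is calculated from the single Visit I height, so that change in BMI reflects change in weight only. Height can then be dropped from Visits II and III in the visit list. Self-reported values need not be excluded from the analysis of change in BMI.

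The cost is one or two lines of text, with no new equipment and no effect on sample size. Two height measurements per participant are saved. The change should be made before further heights are recorded, because coarse values cannot be refined later.

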### Participant timeline {13}

The participant timeline is shown in Table 2.

**Table 2 Tab2:**
[figure not shown]
Schedule for enrollment, intervention, and assessments during the study period

### Sample size {14}

#### Sample size for pilot study

No randomized controlled trials have investigated the combined effect of inulin with ST on periodontal outcomes. To ensure the feasibility of the study—including participant adherence to the protocol and sample collection—a pilot study will be performed. The goal is to obtain data from 20 participants for each group during the pilot study. Assuming that up to 20% of participants may drop out or be withdrawn; we will aim to recruit 24 participants per group, for a total of 48 participants. If no unforeseen difficulties arise in the pilot study, participant data will be part of the full trial.

#### Sample size for full trial

The number of sites with probing depths ≥ 4 mm was used to determine sample size, as ST has been shown to reduce BOP to minimal levels to the point where an adjunct could not increase the effectiveness [3]. Previous literature has reported the mean change in number of sites with probing depths ≥ 4 mm from baseline to an average follow-up of 10.86 weeks is a mean of 81 with a standard deviation of 21 [3]. It has been shown that a high fiber diet can result in a 4% decrease in average PD though these participants were not diagnosed with periodontal disease and were not undergoing treatment with ST [24]. We believe it is reasonable to estimate that participants who are suffering from this disease and have deeper probing depths will experience a greater reduction in PD ≥ 4 mm in combination with ST (10%), as baseline PD is positively associated with follow-up PD [3]. Thus, the estimated mean change in the number of sites with probing depths of ≥ 4 mm is 91. Using a power of 80% and an alpha of 0.05, the total number of participants needed per group is 71. A 20% drop-out rate is estimated; the sample size for the full trial is 85 per group or a total of 170 participants. The sample size needed for the full trial was estimated using a statistical software (G*Power 3.1).

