### Objectives {7}

The primary objective of this trial is to determine if inulin supplementation for 14 weeks, provided pre-, peri-, and post-ST, is more effective than the placebo at significantly decreasing the mean number of sites with PD ≥ 4 mm and decreasing the presence of BOP. Secondary objectives include determining the effects of inulin supplementation pre-, peri-, and post-ST on salivary markers of inflammation and periodontal-associated pathogens.

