### Outcomes {12}

#### Primary outcome measures

Clinical assessment
Reduction in the number of sites with PD ≥ 4 mmReduction in the presence of BOP

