## Statistical methods

### Statistical methods for primary and secondary outcomes {20a}

Data will be entered into excel by a member of the research team. Another member will double-check the numbers and values to ensure the accuracy of data entry. Statistical analyses will be performed using IBM SPSS 26 statistical software and significance will be determined when *P* < 0.05. Mean and standard deviations will be reported for outcomes. Analysis of baseline participant demographics will be calculated to ensure consistency between the groups. The Kolmogorov-Smirnov test will be used to test the normality of the data. Levene’s test will be used to assess the equality of variances. Probing depths outcomes will be analyzed using an independent sample *t* test for the mean change in the number of PD ≥ 4 mm. If the data is not normally distributed, a Mann-Whitney test will be used. BOP is a categorical variable and chi-square analyses will be performed to measure the associations between the presence of bleeding and the treatment group.

The concentrations of the four salivary biomarkers and the quantitative values of the four periodontal pathogens at all three sample collection times will be log transformed to normalize their distribution. Two-way repeated measures analysis of variance (ANOVA) using treatment × time will be used to analyze each biomarker and pathogen individually. A repeated-measures ANOVA with Tukey’s post hoc test will be used to determine changes in energy and macronutrient intakes over the 3 visits in the intervention and control groups.

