This study will contribute to a better understanding of the role of inulin, a type of prebiotic, and periodontal disease. To our knowledge, no direct intervention with prebiotic supplementation to support the effectiveness of ST for periodontal disease has been conducted. Though, there is evidence that a higher intake of dietary fiber supports periodontal health. Dietary fiber may act as a mechanical force on the dental surfaces to aid in the shedding of the periodontal-associated pathogens in the microbial biofilm [35]. We will determine if a supplement can still be effective for periodontal health, given the lack of mechanical force needed for digestion of the inulin supplement to be provided.

This unique study design allows us to measure the response of inulin prior to and after sanative therapy. We can determine if inulin can improve periodontal biomarkers alone and if inulin can be considered an adjunct to ST. Salivary biomarkers are likely to change prior to improvements in clinical outcomes, which is why we are measuring salivary biomarkers and periodontal pathogens but not clinical outcomes at Visit II. The first 4 weeks of the intervention prior to ST will be used to assess the response of inulin alone; we predict that inulin supplementation may be able to decrease salivary markers of inflammation and periodontal-associated pathogens. The remaining 10 weeks will compare ST to ST and inulin supplementation. It is hypothesized that the inulin group will have a greater reduction in the number of sites with PD ≥ 4 mm and for the percentage of sites with BOP. Further, the subgroup analyses are anticipated to show that the response is greater in participants who are overweight/obese.

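### BOP shares primary rank with PD although the sample-size section says an adjunct could not improve it, so the stated 80% power at 5% error holds for PD alone

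*Protocol article*

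**What the plan says.** - **Rank of the outcomes.** The Abstract and Objectives {7} put PD and BOP together in the primary objective. Inulin is to be "more effective than the placebo at significantly decreasing the mean number of sites with PD ≥ 4 mm and decreasing the presence of BOP". Outcomes {12} lists both under the primary outcome measures, with no order between them.
- **Sizing.** Sample size for full trial {14} uses the number of sites with PD ≥ 4 mm only. The reason given is "as ST has been shown to reduce BOP to minimal levels to the point where an adjunct could not increase the effectiveness".
- **Prediction.** The Discussion hypothesizes for inulin a "greater reduction in the number of sites with PD ≥ 4 mm and for the percentage of sites with BOP". It also expects larger BOP reductions in overweight or obese participants than in non-obese ones.
- **Tests.** Statistical methods {20a} sets one threshold for everything: "significance will be determined when *P* < 0.05". PD change is compared by a t test (Mann-Whitney if not normal) and BOP by chi-square.

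**The concern.** The article takes three positions on BOP that do not fit together: it is a primary outcome, an adjunct to sanative therapy (ST) cannot improve it, and inulin is expected to improve it. If the second is right, BOP is a poor primary outcome for an adjunct trial. If it is wrong, the reason for leaving BOP out of the sample size falls away.

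The practical risk comes at the end of the trial. If inulin works on PD and the sizing premise about BOP is true, the likeliest result is a significant PD difference and no BOP difference. The primary objective as worded does not settle whether that is a positive trial. If the answer is chosen after the results are known, neither the error rate nor the power of the conclusion is the one planned.

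**Working it through.** **Inputs from Sample size for full trial {14}:** mean change 81 sites in controls and 91 with inulin, SD 21, power 80%, alpha 0.05, 71 per group. Sidedness is not stated.

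**1. Reproduce the plan's figure.** Difference = 91 − 81 = 10; standardized effect = 10/21 = 0.476.
- Normal approximation: n = 2 × (1.960 + 0.842)² × 21² / 10² = 69.2, so 70 per group.
- Noncentral t, two-sided 0.05: n = 70.2, so 71 per group, as stated. Power at 71 is 80.4%.
- One-sided 0.05: n = 55.2, so 56 per group, which does not match.

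The stated 71 thus gives PD the whole two-sided 0.05 and leaves nothing for BOP.

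**2. If both outcomes must be significant.** No alpha adjustment is needed. Take PD power as 80% and, on the sample-size section's premise, no inulin effect on BOP. The BOP test then favours inulin by chance with probability 0.025.
- Independent tests: 0.80 × 0.025 = 2.0%.
- Bivariate normal, assumed correlation 0.3, 0.5, 0.7: 2.4%, 2.5%, 2.5%.

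The ceiling is 2.5% whatever the correlation, against a planned 80%.

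**3. If either outcome suffices.** Two-sided family-wise error with each test at 0.05:

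| Assumed correlation | Error under no effect on either outcome |
|---|---|
| 0 | 1 − 0.95² = 9.75% |
| 0.5 | 9.1% |
| 0.7 | 8.3% |
| 0.9 | 7.0% |

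These count errors in both directions. Errors in inulin's favour alone, for independent tests, are 1 − 0.975² = 4.9% against 2.5% for a single test, so the ratio is again about two.

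**4. If BOP is close to zero.** Suppose BOP is one yes/no result per participant, with equal rates in both arms and 71 per arm (rates assumed, not in the article). Uncorrected chi-square is then conservative. At 1% it rejects 0.6% of the time and at 2% it rejects 2.6%. With an independent PD test the family-wise error is 1 − 0.95 × (1 − 0.0056) = 5.5% and 1 − 0.95 × (1 − 0.0262) = 7.5%. At a 5% rate it is back near nominal (9.6%).

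**5. What a split of alpha would cost.** With Bonferroni (0.025 each), PD power at 71 per group drops from 80.4% to 71.6%. Restoring 80% needs n = 85.1, so 86 evaluable per group, or 86/(1 − 0.2) = 107.5, so 108 recruited per group.

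**6. What a fixed sequence would cost.** PD is tested first at 0.05, and BOP at 0.05 only if PD is significant. Family-wise error stays at 5%, PD keeps its full alpha, and 71 evaluable per group still suffices.

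**The case against.** **A multiplicity rule usually sits in the SAP, and none is shown.** This stands as far as it goes. The absence of an alpha split or testing order here is not itself the defect. An SAP cannot, however, remove the conflict between statements in the protocol about whether BOP can respond, and the choice of primary outcome is a protocol decision.

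**The inflation belongs to a rule the article never states.** This also stands. A reader might infer that the trial will run at nearly 10% error. The article does not support that: Objectives {7} joins the outcomes with a conjunction, attaches significance explicitly only to PD, and nowhere says that BOP alone would make the trial positive. The 9.75% is conditional on an either-suffices rule, counts errors in both directions, and shrinks if BOP is near zero.

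**A reader might equally infer that the trial cannot succeed.** That is too strong. The premise about BOP is a single clause resting on a cited study, and the Discussion predicts the opposite. Even on that premise, and with both outcomes required, the chance is about 2.0–2.5%, not zero.

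**The sizing clause only explains why PD drove the sample size.** It does so by denying an adjunct any room to improve BOP, and that bears directly on whether BOP can serve as a primary outcome.

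**There is a clinical reason to look at both.** The Background argues that PD and BOP together describe periodontal status and response to ST. That is a good reason to measure and report BOP, but it does not require equal primary rank.

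**Conclusion.** The point holds in this form: the article gives PD and BOP equal primary rank and predicts benefit on both, while its sample-size section denies that an adjunct can improve BOP and commits the full two-sided 0.05 to PD. The figure of 71 per group is correct for PD alone. Neither reading of the primary objective delivers 80% power at 5% error. Requiring both gives about 2.0–2.5% chance of success if inulin leaves BOP unchanged. Accepting either gives a two-sided family-wise error of up to about 9.75%.

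The first result depends on the article's own premise about BOP. The second depends on a decision rule that the article does not state, on assumed correlations, and on BOP not being close to zero. This should be settled before any unblinded comparison, because it decides what the trial may conclude.

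**What to change.** - Make the number of sites with PD ≥ 4 mm the single primary outcome, at two-sided 0.05.
- Make BOP the first secondary outcome, tested confirmatorily only if PD is significant, and otherwise reported descriptively.
- Align the Abstract, Objectives {7}, Outcomes {12}, Sample size {14} and the Discussion. In particular, reconcile the predicted BOP benefit with the statement that an adjunct could not improve BOP. Update the registry entry if it lists both as primary.

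This follows the sponsor's own sizing logic. It costs protocol wording, and possibly a registry update through the amendment route that the article describes; the 71 evaluable per group and the PD power are unchanged. The small downside is that a BOP difference without a PD difference could no longer support a positive conclusion. Other schemes, such as explicit co-primaries or a split alpha, would also settle the error rate. The first would need BOP to be powered, and the second would need more participants (86 evaluable per group with Bonferroni).
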